### **7.3.5 Neuropathy**

Subjects presenting with sensory symptoms lasting more than 5 days or motor symptoms confirmed by physical examinations should be evaluated and non-inflammatory causes such as disease progression, infections (including Lyme disease), metabolic syndromes and medications (such as taxanes and/or platinum salts) should be ruled out. A neurology consult should be obtained and diagnostic characterization of the neurological syndrome (electromyogram, nerve conduction studies) should be started. The next dose of ipilimumab should be skipped if the event of a Grade 2 neuropathy (sensory or motor) is related to study drug. The administration of ipilimumab should be permanently discontinued in patients with Grade 3 or 4 sensory neuropathy suspected to be related to study drug. Patients should be treated according to institutional guidelines and the administration of IV steroids (e.g., methylprednisolone 2 mg/kg once or twice per day or equivalent) should be considered. The administration of ipilimumab should be permanently discontinued in patients with Grade 3 or 4 motor neuropathy regardless of the causality to study drug. Patients with Grade 3 or 4 motor neuropathy who are clinically stable should be treated according to institution guidelines and the administration of IV steroids therapy (e.g., methylprednisolone 2 mg/kg once or twice per day or equivalent) should be considered. Patients with Grade 3 or 4 motor neuropathy who are not clinically stable or who have atypical symptoms should be hospitalized and the IV administration of steroids should be initiated and IV immunoglobulin (IVIg) or other immunosuppressive therapies (as appropriate) should be considered. A neuropathy management algorithm is presented in [Appendix 10](#).

### **7.3.6 Other**

Ocular inflammation (episcleritis or uveitis) was reported in a few subjects. These conditions responded to topical corticosteroid therapy. An ophthalmologist should evaluate visual complaints with examination of the conjunctiva, anterior and posterior chambers, and retina. Visual field testing and an electroretinogram should also be performed. Examination and testing should be documented on the appropriate case report form (CRF). Ipilimumab-related uveitis or episcleritis may be treated with topical corticosteroid eye drops. Symptoms of abdominal pain associated with elevations of amylase and lipase suggestive of pancreatitis may be associated with anti-CTLA-4 monoclonal antibody administration.

The differential diagnosis of acute abdominal pain should include pancreatitis. Appropriate evaluation should include serum amylase and lipase tests.

## Diarrhea Management Algorithm

[figure not shown]

| Diarrhea | GRADE 1                                                                                      | GRADE 2                                                                                                                                                | GRADE 3                                                                                                                                                               | GRADE 4                                           | GRADE 5 |
|----------|-----------------------------------------------------------------------------------------------------|---------------------------------------------------------------------------------------------------------------------------------------------------------------|------------------------------------------------------------------------------------------------------------------------------------------------------------------------------|----------------------------------------------------------|----------------|
|          | Increase of < 4 stools per day over baseline; mild increase in ostomy output compared with baseline | Increase of 4-6 stools per day over baseline; IV fluids indicated < 24 hrs; moderate increase in ostomy output compared to baseline; not interfering with ADL | Increase of ≥ 7 stools per day over baseline; incontinence; IV fluids ≥ 24 hrs; hospitalization; severe increase in ostomy output compared to baseline; interfering with ADL | Life-threatening consequences (eg, hemodynamic collapse) | Death          |

[figure not shown]

**Footnote**

For numbered footnotes (), please refer to further explanation and text found in the corresponding dotted line boxes to the right side of the algorithm

The most current experience with immune-related hepatitis has allowed further development of this management algorithm to include recommendations for treatment.

## HEPATOTOXICITY THERAPEUTIC INTERVENTION ALGORITHM

Situation: rising liver function tests (LFTs) > 8X ULN or suspected immune-mediated hepatitis

- 1) Admit subject to hospital for evaluation and close monitoring
- 2) Stop further ipilimumab dosing until hepatotoxicity is resolved. Consider permanent discontinuation of ipilimumab per protocol (Section 6.2.5 of protocol)
- 3) Start at least 120 mg methylprednisolone sodium succinate per day, given IV as a single or divided dose
- 4) Check liver laboratory test values (LFTs, T-bilirubin) daily until stable or showing signs of improvement for at least 3 consecutive days
- 5) If no decrease in LFTs after 3 days or rebound hepatitis occurs despite treatment with corticosteroids, then add mycophenolate mofetil 1g BID per institutional guidelines for immunosuppression of liver transplants (supportive treatment as required, including prophylaxis for opportunistic infections per institutional guidelines)
- 6) If no improvement after 5 to 7 days, consider adding 0.10 to 0.15 mg/kg/day of tacrolimus (trough level 5-20 ng/mL)
- 7) If target trough level is achieved with tacrolimus but no improvement is observed after 5 to 7 days, consider infliximab, 5 mg/kg, once
- 8) Continue to check LFTs daily for at least 2 weeks to monitor sustained response to treatment

A flow chart of the algorithm is depicted in the following page.

[figure not shown]

[figure not shown]

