## 5.2 Re-Induction Treatment

Patients who have progressed following stable disease (SD) of  $\geq 3$  months duration from Week 12 assessment OR patients who have progressed following an initial response to the induction treatment (CR or PR diagnosed at week 12 assessment) may be offered additional cycles of therapy (4 infusions of ipilimumab 3mg/kg every 3 weeks) with the originally assigned treatment regimen ("Re-induction") until off-treatment criteria are met, provided they meet re-treatment criteria specified below.

- Re-treatment criteria:

Patients who received ipilimumab as induction in this study and have met each of the following criteria within **28 days** before re-treatment, are eligible for "re-induction":

- Had no unacceptable toxicity requiring ipilimumab discontinuation; OR
  - Patients who did not permanently discontinue treatment due to select irAEs as follows:
    - Reversible autoimmune hepatitis
    - Medically manageable endocrinopathy
    - Reversible dermatological toxicity
  - ECOG performance status of 0, 1 or 2
  - Electrocardiogram (ECG): during screening and week 12. Patients with an existing myocarditis are excluded from this study. For patients with suspicion of myocarditis e.g. dyspnoea, functional insufficiency etc. ECG examinations have to be performed before each treatment.
  - Patient must meet all other inclusion criteria as outlined before (see Inclusion criteria)
- AND
- Have experienced disease progression as documented by physical examination or diagnostic imaging (including brain imaging) after demonstrating expanded clinical benefit (see below).

All patients eligible for Re-induction treatment with ipilimumab their TSH level must be assessed at baseline and before each dose and the TSH level be available to the investigator prior to the administration of the dose. **The assessment of TSH is mandatory prior each treatment.** If a subject has thyroid dysfunction and concomitant symptoms (i.e. fatigue), the subject should be monitored more frequently and be treated as per standard medical practice.

The management algorithm for endocrine abnormalities is available on page 59 (appendix 10-15).

- Re-induction treatment:

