During the Re-Induction treatment, subjects enrolled who are eligible for additional treatment cycles will repeat the treatment phase as outlined in INDUCTION TREATMENT. They will receive ipilimumab at the 3 mg/kg dose level every 3 weeks for the first 10 weeks (Weeks 1, 4, 7 and 10) of Re-induction.

Ipilimumab therapy should be offered to all subjects who have not experienced unacceptable toxicity (refractory Grade > 3 irAEs) and are considered by the investigator to be obtaining clinical benefit, either because of apparent tumor stability or continued shrinkage and/or late response. No patient will be re-treated if they experience a Grade 3 or higher nondermatologic autoimmune breakthrough event (ABE) considered related to study therapy or a Grade 3 or higher gastrointestinal or certain other immune-related adverse events (irAE) which require permanent discontinuation of ipilimumab (refer to section 5.5.3). If a patient has experienced a study medication-related dermatologic or non-dermatologic ABE < Grade 3, then the event must have improved to Grade 1 or less before re-treatment can be considered. No patient with disease progression following the first cycle of study medication will be permitted to be re-treated with study medication.

Patients can be eligible for more than one re-induction. The number of re-inductions is not limited. All re-inductions initiated while patient is on-study (**each patient study period**, first dosing + 12 months) will be performed in the frame of the study. Any re-induction starting after each patient study period (first dosing + 12 months) would be done outside of the study.

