### 5.3 Definition of Selected Reversible irAEs that May be Considered For Re-Treatment

Patients with selected irAEs related to ipilimumab that have completely resolved with immunosuppressive therapy or are adequately controlled with hormone therapy, may be considered for further re-treatment with ipilimumab under this study, at the time of disease progression. The list of completely reversible or medically managed immune-related adverse events (irAEs) eligible for consideration is:

- Reversible autoimmune hepatitis
- Medically managed endocrinopathy
- Reversible dermatological toxicity

All other irAEs are not considered eligible for re-treatment, including, but not limited to,

≥ Grade 3 colitis or diarrhea, or uveitis of any grade.

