#### ***Ipilimumab Dose Skipping Rule***

Decisions to skip an ipilimumab dose must be made on specified safety criteria. Treatment with ipilimumab will be skipped or discontinued if the subject experiences at least one adverse event, specified below, considered by the investigator to be **“possibly”, “probably” or “certainly” related to ipilimumab treatment**. The investigator should contact the PI for any adverse event that will prompt a skipped dose or discontinuation of ipilimumab.

The following criteria will be used to determine dose skipping, restarting doses, or discontinuing ipilimumab.

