#### 5.5.3.a *Permanent Discontinuation for Related Adverse Events*

**The following treatment related non-neurological adverse events require permanent discontinuation of ipilimumab:**

- Any  $\geq$  Grade 2 eye pain or reduction of visual acuity that does not respond to topical therapy and does not improve to  $\leq$  Grade 1 severity within 2 weeks of starting therapy, OR, requires systemic treatment.
- Any  $\geq$  Grade 3 bronchospasm or other hypersensitivity reaction.
- Any other  $\geq$  Grade 3 non-skin related adverse event with the exception of events listed under "No Discontinuation" (below).
  - Any  $\geq$  Grade 4 laboratory abnormalities, except AST, ALT, or Total Bilirubin
  - AST or ALT  $> 8 \times$  ULN
  - Total Bilirubin  $> 5 \times$  ULN
  - Any other  $\geq$  Grade 4 adverse event

- Any adverse event, laboratory abnormality or intercurrent illness which, in the judgment of the investigator, presents a substantial clinical risk to the patient with continued dosing.

Please refer to the IB for specific treatment algorithms.

**The following neurological adverse event requires permanent discontinuation of ipilimumab and defines unacceptable neurotoxicity:**

- Any motor neurologic toxicity  $\geq$  Grade 3 regardless of causality
- Any  $\geq$  Grade 3 treatment related sensory neurologic toxicity

Please refer to the IB for specific treatment algorithms.

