**Appendix 7: Patient Information and Informed Consent**

## Appendix 8: irAE Treatment Algorithm

### Re-Induction:

Patients who progress following stable disease of  $\geq 3$  months starting from diagnosis at week 12 tumor assessment duration from beginning of induction treatment or or patients who have progressed following an initial response (partial or complete) assessed at week 12 may be offered additional cycles of therapy with the originally assigned treatment regimen until off-treatment criteria are met, provided they meet re-treatment eligibility requirements. Please note that progressive disease must be confirmed within not less than 4 weeks.

Re-induction is not allowed in patients who experience

- At least one Grade 3 or higher gastrointestinal immune-related adverse events (irAE) including, but not limited to,  $\geq$  Grade 3 colitis or diarrhea **OR**
- Uveitis of any grade **OR**
- At least one certain other immune-related adverse events (irAE) (refer to section 5.2 and 5.3) **OR**
- Disease progression following the first cycle of study medication

Exemption: Re-induction is allowed in patients who experience selected irAEs related to ipilimumab that have completely resolved with immunosuppressive therapy or are adequately controlled with hormone therapy, may be considered for further re-treatment with ipilimumab under this study, at the time of disease progression. The list of completely reversible or medically managed immune-related adverse events (irAEs) **eligible** for consideration is:

- Reversible autoimmune hepatitis
- Medically managed endocrinopathy
- Reversible dermatological toxicity

All other irAEs are not considered eligible for re-treatment!

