### 7.3.2 Liver

Liver function tests should always be performed and reviewed prior to administration of all ipilimumab doses. Patients treated with ipilimumab may develop elevation in LFT in

the absence of clinical symptoms. In addition, subjects presenting with right upper quadrant abdominal pain, unexplained nausea, or vomiting should have LFTs performed immediately and reviewed before administering the next dose of study drug. Any increase in LFT should be evaluated to rule out non-inflammatory causes of hepatotoxicity including infections, disease progression or medications and followed with frequent LFT monitoring at 3-day intervals until resolution.

Any LFTs  $\geq$  Grade 2 (for subjects with normal baseline LFT) or LFT  $\geq$  2 times baseline values (for subjects with baseline LFT of Grade 1 or 2) should prompt treating physicians to: (1) contact the medical monitor; (2) increase frequency of monitoring LFTs to at least every 3 days until LFT have stabilized or improved; (3) investigate to rule out non-irAE etiologies; and (4) initiate an autoimmunity evaluation. Disease progression, other malignancies, concurrent medications, viral hepatitis, and toxic etiologies should be considered and addressed, as appropriate. Imaging of the liver, gall bladder, and bile ducts should be considered to rule out neoplastic or other non-irAE-related causes for the increased LFTs. An ANA, perinuclear anti-neutrophil cytoplasmic antibody (pANCA), and anti-smooth muscle antibody test should be performed if an autoimmune etiology is considered.

If the LFTs are  $> 5$  times the upper limit of normal (ULN) or total bilirubin is  $> 3$  times the ULN, then ipilimumab dosing should be held according to the dose modification guidelines.

Subjects with LFT elevations  $> 8x$  the ULN that are judged to be due to ipilimumab should initiate high-dose corticosteroid therapy (e.g., methylprednisolone 2 mg/kg once or twice daily or equivalent) and permanently stop administration of ipilimumab. In subjects with  $> 8x$  ULN, LFT should be performed daily until stable or declining for

5 consecutive days. LFT should be monitored for at least 2 consecutive weeks to ensure sustained treatment response. If symptoms or LFT elevations are controlled, the corticosteroid dose should be gradually tapered over a period of at least 1 month. Flare in LFTs during this taper may be treated with an increase in the dose of steroid and a slower taper.

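### Hepatotoxicity algorithm step 2 makes optional a permanent stop that Section 5.5.3.a requires for related AST/ALT above 8 x ULN, and Section 5.6.1 bans drugs that the irAE guidance uses

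*Protocol*

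**What the plan says.** **Stopping for liver toxicity.** Section 5.5.3.a opens its list with "The following treatment related non-neurological adverse events require permanent discontinuation of ipilimumab". AST or ALT above 8 x ULN is on the list, as is total bilirubin above 5 x ULN. Section 5.5.3.b, which sets out the exceptions, names none for hepatitis or transaminases. The liver text in Appendix 10-15 (7.3.2) covers elevations above 8 x ULN judged due to ipilimumab; its instruction to start corticosteroids ends "or equivalent) and permanently stop administration of ipilimumab".

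The numbered hepatotoxicity algorithm in the same appendix is triggered by liver tests above 8 x ULN or by suspected immune-mediated hepatitis. For both triggers alike, step 2 reads "Stop further ipilimumab dosing until hepatotoxicity is resolved. Consider permanent discontinuation of ipilimumab per protocol (Section 6.2.5 of protocol".

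**Re-treatment.** Section 5.2 admits to re-induction "Patients who did not permanently discontinue treatment due to select irAEs as follows", and reversible autoimmune hepatitis is one of the events that follow. The same section then states: "No patient will be re-treated if they experience a Grade 3 or higher nondermatologic autoimmune breakthrough event (ABE) considered related to study therapy". That sentence goes on to bar re-treatment after irAEs that require permanent discontinuation, with a pointer to Section 5.5.3. Section 5.3 introduces its own list with "The list of completely reversible or medically managed immune-related adverse events (irAEs) eligible for consideration is", and Appendix 8 has an "Exemption: Re-induction is allowed in patients who experience selected irAEs related to ipilimumab that have completely resolved with immunosuppressive therapy". Both lists include reversible autoimmune hepatitis without a grade limit.

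**Prohibited drugs.** Section 5.6.1 lists immunosuppressive agents and chronic systemic corticosteroids among therapies not to be used during the study. No exception is given, and Section 5.6.2 (restricted therapies) is marked not applicable.

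**The concern.** The algorithm is the page a site is likely to open when transaminases rise. Section 6.2 points to Appendix 10-15 for safety management. Section 5.5.5.c makes the hepatotoxicity algorithm compulsory for abnormal liver tests, although it refers there to the Investigator Brochure. A site that follows step 2 literally could resume ipilimumab, once the tests recover, in a patient whom Section 5.5.3.a takes off the drug for good. The cross-reference does not help, because Section 6.2 is Safety Assessments and has no subsections.

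On rescue drugs, sites meet two opposite rules. Section 12.2 requires significant deviations to be documented in the eCRF, so the same mycophenolate or infliximab course could be logged as a deviation at one site and as directed care at another.

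**Working it through.** No plan figure is in dispute, so the main check is to set the texts side by side.

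**Step 1. Related AST or ALT above 8 x ULN.**

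| Source | Instruction |
|---|---|
| Section 5.5.3.a | permanent discontinuation, mandatory |
| Section 5.5.3.b | no hepatic exception; the general one covers inflammation below Grade 4 from a local anti-tumor reaction |
| Appendix 10-15, 7.3.2 Liver | hold above 5 x ULN; stop permanently above 8 x ULN if due to ipilimumab |
| Hepatotoxicity algorithm, step 2 | hold until resolved; permanent stop to be considered |

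Three places form one consistent scheme and step 2 departs from it. Tying the hold to resolution implies that dosing may restart.

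**Step 2. Where step 2 is correct.** Its second trigger, suspected immune-mediated hepatitis, includes cases below the 5.5.3.a thresholds, and its first trigger includes elevations not caused by ipilimumab. For those, holding and considering is acceptable. The fault is that step 2 does not separate them from related values above 8 x ULN.

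**Step 3. Re-induction.** A patient left on a step 2 hold has not permanently discontinued, and so could appear to pass the first screen in Section 5.2. The later sentence in 5.2 then excludes that patient. It bars related non-dermatologic events of Grade 3 or higher, and it bars irAEs on the 5.5.3 stop list. Appendix 8 sends readers to 5.2 and 5.3. What remains is re-dosing within a course, plus the ungraded hepatitis entries in 5.3 and Appendix 8, which a site might read without 5.2.

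**Step 4. How many patients.** The protocol gives no rate for AST/ALT above 8 x ULN.

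- Hepatic irAEs of any grade at 3 mg/kg in CA184-022 (Table 3, Section 1.3.5.b): 0 of 71. The exact two-sided 95% upper limit is 1 - 0.025^(1/71) = 0.0506. For 200 patients: 0.0506 x 200 = 10.1.
- Cross-check from Table 2, serious liver irAEs over 0.3 to 20 mg/kg: Grade 3 (72) + Grade 4 (32) = 104. Then 104/2901 = 3.58% (exact 95% CI 2.94% to 4.33%), and 0.0358 x 200 = 7.2 (5.9 to 8.7). This assumes that each subject is counted once at worst grade; 104 is below the table's any-grade count of 109.

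The first figure is an upper bound for a wider class of event, with a point estimate of zero. The second includes doses above 3 mg/kg. Neither counts patients actually exposed to the conflict, who are fewer.

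**Step 5. Section 5.6.1 against the irAE text.**

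| Drug | 5.6.1 | Elsewhere in the protocol |
|---|---|---|
| Mycophenolate | banned | added at algorithm step 5; recommended in 7.3.1 with concomitant hepatitis; to be considered in 7.3.2 |
| Tacrolimus | banned | to be considered at algorithm step 6 |
| Infliximab | banned | suggested in 7.3.1 for refractory cases; to be considered at algorithm step 7 |
| Stable hormone replacement such as hydrocortisone | falls under chronic systemic corticosteroids | accepted in 5.5.3.b |

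(7.3.1 and 7.3.2 are the Appendix 10-15 texts.) Sections 5.3, 6.2 and 6.3 also presuppose immunosuppressive treatment of irAEs; the stopping rule in 6.3 names infliximab. The number of patients affected cannot be derived; 7.3.1 says only that refractory cases are infrequent.

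**The case against.** The strongest reply on step 2 is that it defers to the protocol, whose body rule is explicit and is repeated in the same appendix. The appendix is advisory in tone, and the flow charts after the numbered steps are not shown and may state the stop correctly. Part of this stands: a careful reader would find 5.5.3.a and obey it. But the section that step 2 cites does not exist, and a correct chart would leave the numbered text in conflict with the mandatory rule.

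Safeguards also count. Under the dose-skipping rule in 5.5.2, "The investigator should contact the PI for any adverse event that will prompt a skipped dose or discontinuation of ipilimumab". If more than one dose is expected to be skipped, the coordinating investigator must be consulted. The liver text brings in the medical monitor. Section 5.5.5.c sets liver-test limits before each dose, although these delay rather than prevent a restart after recovery. A note in 5.5.3.b, placed under endocrinopathies but worded generally, forbids restarting during systemic corticosteroids. The liver text tapers these over at least a month against a dosing interval of 3 weeks +/- 7 days (14 to 28 days), so at least one dose would normally be lost. These checks make wrongful re-dosing unlikely, and that argument stands.

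Two stronger readings are tempting. A reader might infer that the re-treatment rules leave re-induction open after severe hepatotoxicity. They do not: the bar in 5.2 refers to the 5.5.3 stop list. A reader might also infer that the protocol withholds rescue treatment, or that steroid courses for irAEs breach 5.6.1. The intent to allow rescue is plain from 5.3, 6.2 and 6.3, and a tapered course, as contemplated in 5.5.4 and the appendix, is not clearly chronic use. The firm conflict is with the non-steroid agents and long-term hormone replacement.

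**Conclusion.** Both inconsistencies are in the current text and should be corrected; the severity is minor. For related AST/ALT above 8 x ULN, step 2 is wrong as written. The residual risk is mainly re-dosing within induction, with a smaller one from the ungraded hepatitis lists in 5.3 and Appendix 8. For 200 patients, the 3 mg/kg data are compatible with 0 to about 10 hepatic irAEs of any grade. This assumes that the CA184-022 rate carries over, and only some such events would exceed 8 x ULN. The 5.6.1 problem is a missing exception, and its cost is inconsistent recording of deviations.

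Nothing here supports a claim that the efficacy results are compromised. The primary 1-year survival rate uses every patient who received at least one dose, and Section 9.4 defines no per-protocol population from which a deviation could remove anyone.

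**What to change.** - **Hepatotoxicity algorithm, step 2.** Reword to: *Permanently discontinue ipilimumab for related AST/ALT above 8 x ULN or any other threshold in Section 5.5.3.a; otherwise hold until resolved.* Replace the reference to Section 6.2.5 with Section 5.5.3.a, and check that the flow charts agree.
- **Section 5.6.1.** To the entries on immunosuppressive agents and chronic systemic corticosteroids add: *except when given to treat an irAE or as hormone replacement.*
- **Optional, Section 5.3 and Appendix 8.** Beside reversible autoimmune hepatitis, add a pointer to the re-treatment bar in Section 5.2. Section 5.2 itself needs no change.

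The cost is a few sentences in a clarification or the next amendment, and a letter to sites. No procedures, patients or analyses are added.
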